### Assessment of the Challenges and Barriers in Implementing CMR in the Indian Health Care Setting

FGDs will be conducted among CMR team members, and approximately 10 to 16 in-depth interviews will be conducted with the prescribers whose patients were recruited as the study participants. This would help in understanding prescribers’ and CMR team members’ perceptions and attitudes toward CMR. An FGD via the nominal group technique is a structured variation of a small-group discussion to reach consensus. It gathers information by asking individuals to respond to questions posed by a moderator and then asking participants to prioritize the ideas or suggestions of all group members.

The participants for FGDs will be chosen via a purposive sampling method, that is, team members of CMR. Preferably, 2 FGDs will be conducted among CMR team members at each study site. The total number of participants per FGD will be 4 to 10, and it will be a heterogeneous group depending upon the operational feasibility. Each FGD will be conducted for approximately 40-60 minutes until the data saturation point is reached. The entire proceedings of the FGD will be audio-recorded using an MP3 player after obtaining verbal consent from the participants.

In-depth interviews will be conducted among prescribers, including physicians, intensivists, and senior staff nurses, by using a predesigned interview guide (Multimedia Appendix 1), with topics covering the working process, resources, competences, drug-related problems, intervention effects, and collaboration. Approximately 10-16 in-depth interviews will be conducted per site until the attainment of the data saturation point. Each in-depth interview will be conducted for a minimum of 20-30 minutes. The participants for the in-depth interviews will be selected via a purposive sampling method. The selection of the participants will be considered to ensure representativeness across all professional domains.

### Phase 5: Calculating the Costs Incurred in the Implementation of CMR From a Health System Perspective (Opportunity Costs)

The multitude of health care providers and payment schemes affects the cost of any health service delivered and the estimation methods used, as costs can differ significantly between health centers due to variations in the service type and structure. Accurate cost analysis requires thorough understanding of a health care facility’s functions and financing mechanisms to ensure that all expenses are considered. In this study, a comprehensive case record form will systematically document both direct and indirect costs related to the CMR process. This includes detailed information on the facility characteristics, human resources, infrastructure, equipment, and operational costs, allowing for an extensive evaluation of the economic impact of the CMR process through quantitative and qualitative data collection [11,12].

### Study Variables and Tools

The study variables, namely, patient demographics (name, age, contact information) and medical history, including current and past medical conditions, allergies, and adverse drug reactions, will be collected with the help of a predesigned case record form that includes tools such as the MAI tool, the STOPP/START tool, and the AT-HARM10 tool, which will be used for data analysis. The economic evaluation will be conducted from a health system perspective. Detailed information will be collected on the facility characteristics, human resources, infrastructure, equipment, and operational costs, allowing for an extensive evaluation of the economic impact of the CMR process from a health system perspective. The collected information in the case record forms will also be entered electronically into the Research Electronic Data Capture (REDCap) software (Vanderbilt), improving the data quality and enabling central access to data (since this is a multicentric study).

### Data Management and Statistical Analyses

#### Quantitative Component

The investigators will ensure the completeness, accuracy, and timeliness of data collection. The study sites will enter data in the REDCap software, and case record forms will be scanned in REDCap. The data will be checked for a normal distribution (Kolmogorov-Smirnov test). Student paired 1-sided *t* test will be used to analyze the differences between MAI scores at admission and discharge to determine the effectiveness of CMR, and the chi-square test or Fisher exact test will be used to assess the differences in the frequency distribution. All analyses will be conducted via the SPSS software (version 22.0 for Windows 11; Microsoft), Microsoft Excel 2019, and STATA (version 12; StataCorp LP).

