##### Quantitative Component

The study design was quasi-experimental preinterventional and postinterventional with the following components: (1) costs incurred for the implementation of CMR in Indian health care settings and (2) MAI, reduction in the percentage of inappropriate medications, postdischarge adverse events, and medication-related admissions.

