### Sample Size Estimation and Analysis

The sample size calculation for the assessment of CMR efficacy was based on a previous study [1], which showed that the prevalence of potentially inappropriate medications in the older adult population was 28% in India. We assume that the effect size of the interdepartmental CMR is 10%, power is 80%, and significance level is 5%. The sample size calculation was estimated to be 280 participants. Given that this study will be conducted at 2 different sites, Pondicherry Institute of Medical Sciences and Jawaharlal Institute of Postgraduate Medical Education and Research, 140 participants will be recruited from each site. Universal sampling techniques will be used to enroll participants in this phase of the study. For the qualitative component of the study to assess the implementation challenges of CMR, preferably 2 FGDs will be conducted among CMR team members at each study site. Approximately 10-16 in-depth interviews will be conducted per site until the data saturation point is reached.

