The statistical analysis to evaluate the costs incurred in implementing CMR in the Indian health care setting from a health system perspective includes direct, indirect, and opportunity costs. Data collected from various facilities will be cleaned and entered into a predesigned database. All costs will be standardized to 2025 prices by using the consumer price index for health care services. Descriptive statistics will summarize continuous variables such as salaries and utility costs by using the measures of central tendency (mean, median) and dispersion (SD, IQR), while categorical variables such as facility type will be reported as frequencies and percentages. Comparative analyses will assess cost differences between public and private sector facilities by using independent-sample 1-sided *t* tests for normally distributed data or Mann-Whitney *U* tests for nonnormally distributed data. To explore the predictors of the cost variations across facilities, we will conduct multivariable linear regression with total CMR costs as the dependent variable and facility characteristics, human resources, and infrastructure costs as the independent variables. Interaction terms such as facility type and operational hours will be included to investigate the moderating effects. All statistical analyses will be performed using STATA (version 18), and *P* values less than .05 will be considered as statistically significant.

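### The MAI change and the public-versus-private cost comparison are tested one-sided at 5% without justification, and the cost test has no stated direction

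*Protocol article*

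**What the plan says.** Three places in the protocol article bear on this.

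- **MAI.** Under Data Management and Statistical Analyses, Quantitative Component, the admission and discharge MAI scores are compared with a "Student paired 1-sided" t test, and the stated purpose is to establish whether CMR is effective. Frequencies go to a chi-square or Fisher exact test, with no sidedness given. This paragraph sets no significance threshold.
- **Cost.** The cost paragraph, printed under Qualitative Component, reads "Comparative analyses will assess cost differences between public and private sector facilities by using independent-sample 1-sided" t tests, with Mann-Whitney for non-normal data. It names no expected direction. It ends with a threshold of P<.05, in a sentence that covers all statistical analyses.
- **Sample size.** Sample Size Estimation and Analysis states "power is 80%, and significance level is 5" percent, without saying whether that level is one- or two-sided.

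Under Study Design, "The study design was quasi-experimental preinterventional and postinterventional", and no concurrent control group is described. Secondary End Points defines the MAI end point as a change in score, without a direction. No section gives a reason for one-sided testing or sets a one-sided level of 2.5%.

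**The concern.** A one-sided test needs a direction fixed in advance and a reason why the other direction is of no interest. Neither is given here.

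For cost, the aim is to look for differences between two sectors. A one-sided test of that aim is not defined until someone chooses which sector is expected to cost more. If the choice is made once the data are visible, the real error rate is double the nominal one.

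For MAI, the direction can be guessed (improvement), but two consequences follow. All of the 5% error sits on the side that favours CMR, in a design where any time trend already counts towards the intervention. And if the score worsened between admission and discharge, the planned test could not call that significant, however large the change.

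**Working it through.** **1. Error rates of the tests as written**

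| Test | Critical z | Error for a favourable MAI result |
|---|---|---|
| One-sided 5% (as written) | 1.645 | 0.05 |
| Two-sided 5% (conventional) | 1.960 | 0.025 |

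The ratio is 0.05 / 0.025 = 2. For cost with no direction fixed, choosing the tail after seeing the data rejects when |z| > 1.645, so the error is 0.05 + 0.05 = 0.10.

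**2. What level lies behind the 280?**

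Inputs from Sample Size Estimation and Analysis: "the prevalence of potentially inappropriate medications in the older adult population was 28% in India"; an assumed CMR effect of 10%, read here as an absolute fall from 0.28 to 0.18 (an assumption); power 80% (z = 0.842); level 5%. Stated result: "The sample size calculation was estimated to be 280 participants".

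*Two proportions, pooled variance under the null hypothesis*

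n per group = [z_α √(2 p̄ q̄) + z_β √(p₁q₁ + p₂q₂)]² / d², with p̄ = 0.23 and d = 0.10. The roots are √0.3542 = 0.5952 and √0.3492 = 0.5909.

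- Two-sided: (1.960 × 0.5952 + 0.842 × 0.5909)² / 0.01 = 276.8, so 277.
- One-sided: (1.645 × 0.5952 + 0.842 × 0.5909)² / 0.01 = 217.9, so 218.

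*McNemar, before and after taken as independent*

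Discordant share ψ = 0.28 × 0.82 + 0.72 × 0.18 = 0.3592, and n = [z_α √ψ + z_β √(ψ − d²)]² / d².

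- Two-sided: 279.6, so 280.
- One-sided: 220.0, so 220.

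The 280 is therefore reproduced at a two-sided 5% level. At a one-sided 5% level the same inputs fall 21% to 22% short of it (220/280 = 0.786; 218/280 = 0.779).

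**3. How firm is that inference?**

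It depends on choices that the article does not state.

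- A smaller discordant share changes the two-sided McNemar figure: 194 at ψ = 0.25 and 155 at ψ = 0.20.
- A one-sided 5% calculation also reaches 280 with an unstated dropout of about 22% (218 / 0.78 = 279.5), or with a discordant share of about 0.455.
- The 277 is a per-group figure for two independent groups, which this design does not have.

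The result is consistent with a two-sided level but does not prove it.

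**4. What two-sided testing costs for MAI**

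Detectable standardised change with n = 280 pairs and 80% power ≈ (critical value + 0.842) / √280, with √280 = 16.73 and t critical values on 279 degrees of freedom:

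- One-sided 5%: (1.650 + 0.842) / 16.73 = 0.149 SD.
- Two-sided 5%: (1.969 + 0.842) / 16.73 = 0.168 SD.

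The loss is about 0.019 SD.

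**The case against.** The best defence is that CMR is meant to reduce inappropriate prescribing, so the MAI hypothesis has an evident direction. MAI and cost are also secondary end points (the primary end point concerns facilitators and barriers), and a rise in MAI would still show in the reported means. This stands as far as it goes: the MAI test has a discernible direction, and only the formal claim of worsening is lost. It does not justify putting the full 5% in one tail, and it does not help the cost test, for which no direction can be inferred.

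A second defence is that P<.05 closes the cost paragraph, which names different software from the MAI paragraph. Applying it to MAI is therefore a reading. It is a reasonable one, because the sentence covers all statistical analyses and the sample size section also uses 5%.

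Some stronger readings are tempting, and the article does not support them:

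- **That 280 can only come from a two-sided level, so the test is twice as lenient as its own sizing.** Sidedness, formula, pairing and dropout are all unstated. Moreover, "The sample size calculation for the assessment of CMR efficacy was based on a previous study" of potentially inappropriate medications, not of MAI or cost, and the tests for frequencies are not labelled one-sided.
- **That MAI is likely to rise as drugs are added in hospital or START suggestions are accepted.** The article does not describe how MAI is scored.
- **That the Mann-Whitney fallback is run at a different level.** A missing label in a condensed article is silence, not a contradiction.
- **That cost worsening cannot be shown.** The problem of undetectable worsening belongs to MAI; for cost the problem is the missing direction.

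**Conclusion.** The point holds in a limited form. Both t tests are specified as one-sided at an apparent 5% level with no reason given.

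- **Cost** is the clearer defect: the hypothesis is undefined, and the error rate is 10% if the tail is chosen from the data.
- **MAI**: the false-positive rate for improvement is 5% against the conventional 2.5%, in an uncontrolled design, and worsening cannot be declared significant. This assumes that the P<.05 threshold applies to MAI and that the untested tail is worsening.

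The agreement of 280 with a two-sided 5% level supports the change but does not show that the plan contradicts its own sizing. Nothing here says that N is wrong. The point should be corrected, but it concerns secondary end points and does not undermine the study.

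**What to change.** - In the Quantitative Component paragraph and in the cost paragraph, replace the one-sided t tests with two-sided tests at 5%, and report 95% confidence intervals for the MAI change and the cost difference.
- In Sample Size Estimation and Analysis, state that the 5% level is two-sided.

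A one-sided 2.5% level for MAI would match the conventional error rate but still could not declare worsening, so two-sided is the better choice.

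The change is one of wording. P values for effects in the expected direction become larger (doubled for the same t statistic), and the detectable MAI change rises from about 0.149 to 0.168 SD. N and data collection are unaffected.

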#### Follow-Up Phase

At discharge, the clinical pharmacist will assess the discharge prescription for the MAI score and potentially inappropriate medications. The percentage of acceptance of the suggestions given (by the CMR team during the admission) by the clinicians will also be recorded from the patient records. After discharge, the patients will be telephonically followed up by a trained field investigator for 30 days to inquire about any hospital admissions, visits to the emergency department, drug-related complications, and episodes of dizziness and falls. The AT-HARM10 tool will be used to identify the medication-related hospital admissions after discharge after obtaining the necessary permission from the authors. The detailed description of the study evaluations/measurements/assessments at various time points after CMR intervention is shown in Table 1.

A comparison of MAI scores and the incidence of potentially inappropriate medications before and after CMR intervention at admission and at discharge will predict the efficacy of CMR.

**Table 1 table1:** Description of the study evaluations/measurements/assessments after collaborative medication review intervention.

Event time points			Hospital admission (day 1)		During hospitalization (every third day until discharge)		Hospital discharge		
							Day X^a^		Day 30^b^

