#### Secondary End Points

The secondary end points were as follows:

Costs involved in the implementation of CMR in Indian health care settings (tertiary health care settings perspective).Change in the number of potentially inappropriate medications from hospital admission to discharge due to CMR.Change in the MAI score from hospital admission to discharge due to CMR.Number of medication-related hospital admissions from the day of discharge to 30 days post discharge.

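### The only tests named for frequencies assume independent groups, but PIM occurrence at admission and discharge is compared in the same patients

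*Protocol article*

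**What the plan says.** All places are in the Protocol article.

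- **Design** (Study Design, Quantitative Component): "The study design was quasi-experimental preinterventional and postinterventional". No control group is described. The 140/140 split under Sample Size Estimation and Analysis is by site, not by arm.
- **Efficacy comparison** (Follow-Up Phase): "A comparison of MAI scores and the incidence of potentially inappropriate medications before and after CMR intervention at admission and at discharge" is what is to show efficacy. Table 1 has the same patients screened with STOPP/START and MAI at admission, every third day and at discharge.
- **Sample size** (Sample Size Estimation and Analysis): the basis is that "the prevalence of potentially inappropriate medications in the older adult population was 28% in India", with "effect size of the interdepartmental CMR is 10%, power is 80%, and significance level is 5" percent. "The sample size calculation was estimated to be 280 participants".
- **End point** (Secondary End Points): "Change in the number of potentially inappropriate medications from hospital admission to discharge due to CMR".
- **Tests** (Data Management and Statistical Analyses, Quantitative Component): the MAI score at admission and discharge gets a paired t test. For everything categorical, "the chi-square test or Fisher exact test will be used to assess the differences in the frequency distribution". No outcome and no time points are attached to that clause.

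**The concern.** Each patient contributes a PIM status at admission and another at discharge, and the two are likely to be correlated. Chi-square and Fisher exact tests treat the rows of a table as different people. Two tables could be built from these data, and neither suits the question:

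- **Stacked table** (280 admission observations against 280 discharge observations): the pairing is ignored. With positive correlation the standard error of the change is too large, and the test rejects too seldom.
- **Cross-table** (admission status by discharge status): the test asks whether the two statuses are associated. They would be even if the intervention did nothing.

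At stake is the P value for the one quantitative outcome with a stated sample size, and one of the two comparisons on which the article rests efficacy. The article recognises the pairing for MAI, so the gap for PIMs looks like an oversight.

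**Working it through.** **Inputs.** From the article: p1 = 0.28, a 10% effect read as 10 percentage points (p2 = 0.18), power 80%, alpha 5% (taken as two-sided), N = 280. Not in the article, so assumed: within-patient correlation phi between 0.2 and 0.5, with 0 as reference.

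**Step 1: reproduce the 280.**

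- Two independent proportions, pooled variance, mean proportion 0.23: n = (1.96·√(2·0.23·0.77) + 0.8416·√(0.28·0.72 + 0.18·0.82))² / 0.10² = 276.8, so 277 per group.
- McNemar with phi = 0: discordant cells 0.28·0.82 = 0.2296 and 0.18·0.72 = 0.1296, sum 0.3592. n = (1.96·√0.3592 + 0.8416·√(0.3592 − 0.01))² / 0.01 = 279.6, so 280.

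Both land at or near 280, and both treat the two measurements as independent. The figure is reproduced, but it does not show which test was intended.

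**Step 2: standard error of the change under pairing.** The probability of a PIM at both times is p11 = p1·p2 + phi·√(p1(1−p1)·p2(1−p2)). The discordant cells are p10 = p1 − p11 and p01 = p2 − p11. Then:

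- unpaired SE = √[(0.2016 + 0.1476)/280] = 0.0353
- paired SE = √[(p10 + p01 − 0.10²)/280]

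| phi | p10 | p01 | Paired SE | Unpaired ÷ paired |
|---|---|---|---|---|
| 0 | 0.2296 | 0.1296 | 0.0353 | 1.00 |
| 0.2 | 0.1951 | 0.0951 | 0.0316 | 1.12 |
| 0.3 | 0.1779 | 0.0779 | 0.0296 | 1.19 |
| 0.5 | 0.1434 | 0.0434 | 0.0251 | 1.41 |

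**Step 3: type I error and power of the stacked chi-square** (no continuity correction, nominal two-sided 5%, 280 pairs, 200,000 simulated trials per setting). Type I error is at 28% on both occasions; power is at 28% to 18%.

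| phi | Type I, chi-square | Type I, McNemar | Power, chi-square | Power, McNemar |
|---|---|---|---|---|
| 0 | 4.9% | 4.8% | 80.7% | 80.5% |
| 0.2 | 2.9% | 5.1% | 83.4% | 88.5% |
| 0.3 | 1.9% | 5.0% | 85.2% | 92.3% |
| 0.5 | 0.6% | 4.9% | 89.0% | 98.1% |

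The power differences at phi 0.2, 0.3 and 0.5 are 5.1, 7.1 and 9.1 points. As a check on the type I column: with equal margins the true variance is (1 − phi) times the unpaired one, so the actual size is about 2·(1 − Φ(1.96/√(1 − phi))). This gives 2.8%, 1.9% and 0.6%.

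**Step 4: chi-square on the cross-table with no change** (28% at both times). The noncentrality is about N·phi²: 280·0.04 = 11.2 at phi 0.2 and 280·0.09 = 25.2 at phi 0.3. In simulation the test is significant at 5% in about 91% of trials at phi 0.2, and in over 99% at 0.3 and 0.5.

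**The case against.** **The article does not assign chi-square to PIMs.** This is correct. The clause names no outcome, and valid uses exist, such as comparing the two sites on acceptance of suggestions or on 30-day medication-related admissions. The link is an inference, but a firm one. The Follow-Up Phase section names two efficacy comparisons, MAI and PIM incidence. The analysis sentence gives a paired test for the first and then turns to frequencies. PIM incidence is the only before/after frequency comparison in the efficacy analysis, and no other categorical test is available for it.

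**The stacked error is conservative, and the study keeps its power.** This stands. A reader might infer that the study is underpowered because of the test. The figures do not support that: at the stated effect, power exceeds 80% at every phi examined. The loss is only relative to a paired test. Larger losses can be produced with a smaller assumed effect, but the article states none.

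**The 280 might show that a paired test was planned.** It does not. The McNemar formula gives 280 only at zero correlation (199 at phi 0.3, 145 at 0.5), and the two-sample formula gives 277.

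**No test is named for the PIM count.** A condensed article may leave that to the full protocol or analysis plan, so it is not a defect here. It belongs in the fix only because the same sentence is being edited.

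**PIM change is secondary, and the data stay paired.** This also stands. The primary end point is facilitators and barriers, and a paired test can still be chosen at analysis. This lowers the severity but does not make the named tests suitable.

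**Conclusion.** The point holds as a should-fix. For the before/after PIM comparison, the only candidates the article names are tests for independent groups, in a design where every comparison over time is within patient.

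The harm depends on which table is used, and the article does not say. On the stacked table the result is a conservative test and a moderate loss of efficiency, with the planned power kept. On the cross-table, a significant result would say nothing about change and could be misread as efficacy.

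These sizes rest on phi between 0.2 and 0.5, which the article does not give, on reading the effect as 10 percentage points, on two-sided 5%, and on the patient (any PIM, yes or no) as the unit. At phi = 0 the stacked test and McNemar's test perform alike.

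**What to change.** In the Quantitative Component of Data Management and Statistical Analyses:

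1. For the proportion of patients with at least one PIM at admission versus discharge, name McNemar's test (exact if discordant pairs are few), with the paired risk difference and its 95% CI. This matches the prevalence on which the 280 is based.
2. For the listed change in number of PIMs per patient, name a paired method, such as the Wilcoxon signed-rank test or a repeated-measures count model.
3. Restrict chi-square and Fisher exact tests to comparisons between different patients, such as site versus site.
4. If the percentage of inappropriate medications listed under Study Design is analysed per drug, account for clustering of drugs within patients. A patient-level McNemar test does not cover that measure.

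The cost is a few sentences. No new data, visits or patients are needed, because both measurements are already collected on the same patients.
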